#### Interviews with participants

3.2.2

Like the interviews with the ambassadors, those with TANM’s participants aim to explore their experiences with TANM, focusing on how and which intervention components and contextual factors influence TANM’s observed and experienced short-term outcomes. These interviews will address the same CMO-configurations explored in the interviews with the ambassadors (see Tables 1, 2).

We will interview two types of participants; (1) Those identified as informal caregivers and who attended Phase 2, the peer educational cycle, and Phase 3, the tailored follow-up support; and (2) participants who only took part in Phase 2.

#### Observations

3.2.3

The observations aim to document how the peer educational sessions are delivered, with a focus on contextual factors and mechanisms. We will look at mechanisms, such as providing informational support and discussing individual experiences, and contexts, such as group dynamics and alternative explanatory models of mental illnesses. See Tables 1, 2 for a full overview of the related CMO-configurations.

Observations were conducted using a semi-structured observation guide, designed to capture context and mechanisms from the initial program theory (e.g., social support based on Cohen & Wills (40), aspects of peer education based on Voorham (32)). Specifically, we will focus on:

*Social influences*: References to cultural norms, values, and alternative explanations for mental illnesses; individual experiences shared by participants or ambassadors.*Social support*: Types of social support observed and the ways in which they are expressed.*Role of the ambassador*: Adaptations of content by the ambassador (e.g., translation or cultural tailoring); peer education aspects such as similarity and professionalism.*Group dynamics*: Interactions, trust, inclusivity, dominance of specific members, and both verbal and nonverbal communication.

The guide includes space for additional notes and researcher reflections after observations (full guide is added in Supplementary material II).

The observations will take place during Phase 2 of TANM, with at least one session per intervention group observed by researchers who are fluent in the language spoken in each group. This ensures an accurate understanding of what is observed. Given the expected sensitivity of the topic and the potential caution of participants toward outsiders like researchers, we made efforts to minimize interference with the natural flow of the educational sessions. Accordingly, we schedule our observations to coincide with planned visits from TANM’s coordinating organizations’ representatives. As such, we observe all final sessions, as we are present to administer the questionnaire (see 3.2.4). Additionally, if an organizational visit is planned during the first or second peer education session, we join these visits, observing these sessions as well. This will total to at least 10 observations from the final peer education session, added by one to 10 observations from the first or second sessions. This will result in at least 10 observations of the final peer education sessions, with an additional one to 10 observations from the first or second sessions.

#### Questionnaire

3.2.4

The quantitative component of this study is of exploratory nature and involves the use of a post-intervention questionnaire conducted among participants of the peer education sessions. It aims to capture differences between participant groups, and it will collect insights into the context and mechanisms related to social support, perceived stigma, group composition, and group dynamics (see Tables 1, 2).

All Phase 2 participants are asked to complete the questionnaire at the end of the final third session. Based on advice of the coordinating organizations, we address practical challenges associated with the target group, such as expected language barriers, diverse backgrounds, and varying literacy levels, the questionnaire was simplified to a maximum B2-level in Dutch. We minimized the number of questions and made answer options straightforward (e.g., yes/sometimes/no) to avoid confusion.

At the end of the third session, the attending researcher distributes paper questionnaires and explains the study’s goal, questionnaire, and informed consent, and instructs participants to complete them individually. In groups where participants do not understand Dutch, a research assistant fluent in the group’s language translates each question aloud, one at a time, for the entire group. This approach allows participants to listen to the translation and fill in their responses individually.

Rather than relying on pre-validated questionnaires, the items were constructed based on theoretical concepts from our CMO-configurations. The questionnaire starts with demographic questions (i.e., age, gender, country of birth of the participant and their parents), and questions related to caregiving responsibilities (i.e., frequency and care recipient). It is followed by section on group composition (specifying familiarity and relationships with group members and ambassador prior to the intervention), social support mechanisms (inspired by Cohen and Wills (40)), and mental health taboos and group dynamics. Lastly, an open-ended section allows participants to share lessons or insights gained during the intervention. Table 3 provides an overview of the themes and items, with the full questionnaire available in Supplementary material III.

**Table 3 tab3:** Overview of questionnaire themes, items and example questions.

Questionnaire themes	Number of items	Examples of items and answer options
Group composition	5	Did you know the other participants before the start of the sessions? Answer categories: yes/no. If yes, where from? Answer categories: previous training, church, (volunteer) work, common friends or acquaintances, neighborhood or district.
Social support mechanisms	5	Can you talk to the other group members when you do not feel well or need support? Answer categories: yes/sometimes/no
Mental health taboos and group dynamics	4	Did your group members talk about their experiences with caring for a loved one? Answer categories: yes/sometimes/no

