Once selected, ambassadors receive specialized training, covering three main areas: (1) basic knowledge of mental health conditions, such as depression, psychosis and schizophrenia, which includes symptoms, causes, treatment options and the effects of medication and substance use; (2) informal caregiving, including definitions, perceptions, signs of caregiver burden, and available support services; and (3) practical skills in peer education, such as presentation techniques and an introduction of the content of the peer education sessions. The training is delivered in the Dutch language by a prevention specialist with a background in psychology, a Family Experience Expert (FEE; explained in Section 2.1 about Phase 3) and a caregiver support coach affiliated with the local caregiver support service, which has been part of TANMs coordinating organizations since 2023. The training is highly interactive and fosters a culturally sensitive approach by encouraging ambassadors to share personal experiences and explanatory models they are familiar with. A key message throughout the training is that differing perspectives on mental health conditions can coexist, and that creating space for these perspectives during the peer education sessions is essential.

After completing the training, ambassadors recruit participants for their groups and lead the intervention’s peer education sessions in the dominant language spoken within their group. This could be Dutch, but also, for example, Arabic or Turkish. Ongoing support is provided to the ambassadors in two ways, through regular feedback meetings with members of the coordinating organizations and fellow ambassadors, and through direct access to a designated contact person within the coordinating organizations who is available for individual questions, support or guidance through phone, messaging or in-person contact.

Our evaluation will focus on the current round of TANM (September 2024 – March 2025), which is co-organized by four partners, following the addition of a helpline and support service for caregivers in Rotterdam in 2023.

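### Questionnaire items are read aloud only in groups that do not understand Dutch, so weak readers in Dutch-language groups complete a form of up to B2 level individually, and delivery mode differs between the groups being compared

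*Protocol article*

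**What the plan says.** Section 3.2.4 (Questionnaire) lists the practical challenges of the target group: "such as expected language barriers, diverse backgrounds, and varying literacy levels". The written remedies are wording ("the questionnaire was simplified to a maximum B2-level in Dutch") and brevity: "We minimized the number of questions and made answer options straightforward (e.g., yes/sometimes/no) to avoid confusion".

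Administration takes place at the end of the third session. By default, "the attending researcher distributes paper questionnaires and explains the study’s goal, questionnaire, and informed consent, and instructs participants to complete them individually". There is one exception: "In groups where participants do not understand Dutch, a research assistant fluent in" that group's language gives a spoken translation of the items, one question at a time for the whole group, while participants mark their own forms.

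Section 2 (Intervention description) says that ambassadors "lead the intervention’s peer education sessions in the dominant language spoken within their group", and gives Dutch as one of the possible languages. Section 4.1 adds that the written form existed only in Dutch and that spoken translation was provided when possible, by a researcher or a willing bilingual participant.

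Section 3.3.2 uses the answers to compare groups. The context variables are prior acquaintance with other participants or the ambassador, and the cultural homogeneity of the group. The method is crosstabulation with chi-square tests.

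**The concern.** Language and literacy are different barriers, and section 3.2.4 lists them separately. Oral delivery depends on whether the group understands Dutch, not on whether its members can read the form. A caregiver who follows spoken Dutch but reads it poorly is therefore left with a self-completed form whose language may reach B2.

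Two things are at stake.

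- **Answer quality.** Weak readers in Dutch-language groups may misread items or leave them blank. Section 3.3.2 analyses missing answers as they are, or fills them in from the same person's other answers. That is little protection when the same reading difficulty affects those other answers.
- **Comparability.** The questionnaire is meant to show differences between groups, and delivery mode is set at group level. If culturally mixed groups more often share Dutch as their common language, mode would run alongside cultural homogeneity, one of the planned independent variables. A difference in comprehension could then be read as a context effect. That link is an inference; the documents do not state it.

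**Working it through.** **1. Does the text cover weak readers of Dutch?**

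| Challenge named in 3.2.4 | Remedy described |
|---|---|
| Language barrier | Oral translation, in groups that do not understand Dutch |
| Varying literacy | Wording at B2 or below, few items, simple answer options |
| Varying literacy in a Dutch-language group | The same written remedies and a general explanation by the researcher; no reading aloud described |

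Section 2 allows Dutch-language groups, so the last row is a case that the plan foresees. Section 4.1 discusses translation and interpretation bias but not this case.

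**2. The plan's own sample size.** Section 3.3.2 gives an effect size of 0.4 and about 60 completed surveys. It does not state the metric, alpha, power or degrees of freedom. I assume Cohen's w, alpha 0.05 and 80% power. A 2x3 table (yes/no by yes/sometimes/no) has 2 df and a critical value of 5.991. Power is the probability that a noncentral chi-square variable with noncentrality N × w² exceeds that value. Solving for 80% gives N = 60.2, which reproduces the plan's figure. With 1 df the result is 49.1 and with 3 df it is 68.1, so 2 df is the reading that fits.

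**3. How many forms might be affected.** The documents give neither the number of Dutch-language groups nor the share of weak readers. Assumptions: 3 to 7 of the 10 groups use Dutch, each has about 10 participants (Table 2), and 10-30% of these read the form poorly.

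- Low: 3 × 10 × 0.10 = 3 forms of about 100, or 3%
- Middle: 5 × 10 × 0.20 = 10 forms, or 10%
- High: 7 × 10 × 0.30 = 21 forms, or 21%

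**4. Effect on power.** Suppose a share e of forms carries no information and is spread evenly over the context variable. Then w becomes 0.4 × (1 − e).

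| e | w | N × w² at 80 | Power at 80 | N × w² at 100 | Power at 100 |
|---|---|---|---|---|---|
| 0 | 0.400 | 12.80 | 90% | 16.00 | 96% |
| 3% | 0.388 | 12.04 | 88% | 15.05 | 94% |
| 10% | 0.360 | 10.37 | 83% | 12.96 | 91% |
| 21% | 0.316 | 7.99 | 72% | 9.99 | 81% |

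These figures treat answers as independent and describe one test. They cover only the loss from noise. A mode difference that tracks a context variable would produce bias, which could go in either direction, and the documents give nothing from which to size it.

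**The case against.** The case on the other side has real weight.

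- B2 is a ceiling, not the level of each item. The examples in Table 3 are short, concrete questions with two or three answer options.
- A researcher is present and explains the form. Completing it individually does not rule out help on request. This stands: participants are not abandoned. But help on request is not described, and it depends on a weak reader asking in front of the group.
- The contrast with translated groups is not absolute, since section 4.1 limits translation to when it was possible. This also stands. It makes delivery mode less uniform, which is a further reason to record it.
- The component is exploratory. All four configurations that it covers (1a, 1b, 4a, 4b) are also covered by interviews, and three of them (1a, 1b, 4b) by observations. This limits the consequence.

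A reader might infer that the form cannot reliably measure support and taboo among weak readers. The documents do not support that: they contain no reliability result, no literacy data and no count of Dutch-language groups. A reader might also infer that power drops to 60%. That figure needs 30% of all 80 forms to be uninformative (w = 0.28). Under the assumptions above, 30% is the highest share within Dutch-language groups only; over all forms the share is at most 21%.

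**Conclusion.** The point holds as a risk, not as a demonstrated failure. The administration rule addresses the language barrier but gives poor readers in Dutch-language groups no oral route, although literacy is one of the plan's own stated challenges. It also makes delivery mode a group-level characteristic in a questionnaire meant to compare groups.

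On the assumed 3-21% of forms, the loss of power is small to moderate: from 90% to between 88% and 72% at 80 forms. At 100 forms power stays above 80% throughout. This treats every affected form as carrying no information at all, which is a worst case for those forms. The possible confusion of mode with cultural homogeneity rests on the unstated premise that mixed groups more often use Dutch. It is plausible and should be checked, not assumed.

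**What to change.** Change the rule in section 3.2.4 so that in every group, Dutch-language groups included, each question and its answer options are read aloud one at a time while participants mark their own form. Record for each group the language and mode of administration, so that mode can be set against the context variables when the crosstabulations are interpreted. Where third sessions have already been held, note the mode used in each group and report the difference as a limitation.

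The cost is low. A researcher already attends every final session (section 3.2.3), and the three themes in Table 3 hold 5 + 5 + 4 = 14 items besides the demographic, caregiving and open questions. Expect a few extra minutes in Dutch-language groups, and a fixed pace for fast readers.

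Dictating the open answer to the researcher should at most be optional. It would help weak writers in any group, but it reduces privacy on a subject where section 3.2.3 expects participants to be cautious toward outsiders.

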#### Phase 2 - peer education sessions

2.1.2

Peer educators facilitate three structured sessions, focusing on topics such as understanding mental health issues, the role and challenges of informal caregiving, and available support options. Detailed session topics and objectives are outlined in Appendix I. Ambassadors identify participating informal caregivers who may need additional professional support and refer them Phase 3.

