#### Quantitative data: questionnaire

3.3.2

Quantitative data from the post-intervention questionnaire will be analyzed using SPSS [Version 29.0.0.0; (44)] to examine differences across intervention groups and assess the potential influence of contextual factors on perceived mechanisms and outcomes. Based on the initial program theory, we expect differences between groups (i.e., whether participants knew each other or their ambassador beforehand and the cultural homogeneity of the group), which may influence social support and group dynamics (such as sharing personal experiences with caregiving and/or mental illness and perceptions of taboo). To explore these potential mechanisms within our program theory, we will conduct crosstabulations of these independent and dependent variables, supplemented by chi-square tests to assess the statistical significance of observed differences.

Based on previous studies on peer education with migrants [e.g., (45, 46)], we estimate an effect size of 0.4. Using a power analysis in R (47) with the pwr package (48) we expect to need around 60 completed surveys to achieve sufficient power. Given that we anticipate collecting around 8–12 questionnaires per intervention group, totalling approximately 80–100 questionnaires, we expect to have adequate power for our questionnaire analysis.

Missing data will be included in the analyses as is, unless responses to other questions suggest that the omission can be reasonably filled in based on available information. In such cases, missing responses may be assessed using other relevant data from the same participant. All decisions regarding missing data will be reported transparently in the final analysis.

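### The printed sharing item describes the group while acquaintance is asked of the respondent, so the planned respondent-level chi-square either misses an effect or over-rejects

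*Protocol article*

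**What the plan says.** The quantitative plan crosses contextual factors with perceived mechanisms. In section 3.3.2 the independent variables are "whether participants knew each other or their ambassador beforehand and the cultural homogeneity of the group". The dependent variables are social support and "group dynamics (such as sharing personal experiences with caregiving and/or mental illness and perceptions of taboo". Crosstabulations are to be "supplemented by chi-square tests to assess the statistical significance of observed differences".

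Table 3 (section 3.2.4) prints one example item for each side of that contrast:

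- Acquaintance: "Did you know the other participants before the start of the sessions? Answer categories: yes/no".
- Sharing: "Did your group members talk about their experiences with caring for a loved one", answered yes/sometimes/no.

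Section 3.3.2 takes an effect size of 0.4, states a need for around 60 completed questionnaires, expects 8–12 per group and 80–100 in all, and concludes that power is adequate. Table 2 puts this at 10 ambassadors with about 10 participants each. Table 3 gives examples only: the theme on taboos and group dynamics has four items, and the full questionnaire is in Supplementary material III. Section 3.2.4 calls the quantitative part exploratory.

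**The concern.** The two items sit at different levels. The exposure belongs to the respondent; the outcome belongs to the rest of the group. If people who know others open up more, that effect lies in the respondent's own behaviour, which this item does not record. Each respondent is left out of their own answer, and everyone in a group describes almost the same set of people.

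Two errors can follow. In groups that mix acquainted and unacquainted members, a real effect would appear as no difference. Where whole groups differ in acquaintance, one lively or quiet group contributes about ten near-identical answers, which the test counts as about ten independent observations. The result then enters the triangulation in section 3.3.3 with a significance label that it has not earned.

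**Working it through.** **The plan's own figure.** The article gives neither alpha nor target power; 0.05 and 80% are assumed, and 0.4 is read as Cohen's w. Power is that of a noncentral chi-square with noncentrality N × w². With 2 degrees of freedom (acquaintance yes/no by yes/sometimes/no), 80% power needs N = 61, which matches the stated figure of around 60. Power is then 90% at N = 80 and 96% at N = 100. All of this assumes independent answers.

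**Why the item cannot track acquaintance within a mixed group.** Take a group of ten with five acquainted members, and assume personal sharing of 60% if acquainted and 30% if not. The expected number of *other* members who share is:

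- for an acquainted respondent: 4 × 0.6 + 5 × 0.3 = 3.9;
- for an unacquainted respondent: 5 × 0.6 + 4 × 0.3 = 4.2.

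A 30-point difference in own sharing becomes 0.3 of a person, in the wrong direction.

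**Simulation.** 10 groups of 9 (N = 90), Pearson chi-square at 0.05, 3,000 runs per scenario. The article gives no sharing rates, so all of them are assumptions. The printed item is read in two ways: any/none (at least one other shared), and graded (none; some but fewer than half; at least half). Runs in which all answers are identical count as no rejection.

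*Acquaintance varies within groups (each member 50:50):*

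| Sharing, unacquainted v acquainted | Own-sharing item | Printed item, any/none | Printed item, graded |
|---|---|---|---|
| 10% v 30% | 68% | 7% | 8% |
| 20% v 50% | 86% | 2% | 6% |
| 30% v 60% | 83% | 0.5% | 7% |
| 40% v 80% | 98% | 0.1% | 10% |

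With ten per group (N = 100), and 10% v 40% added to the first three scenarios, the ranges are about 0–8% for the printed item and about 73–96% for an own-sharing item.

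*Acquaintance varies only between groups (five groups acquainted, five not):*

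| Sharing, unacquainted v acquainted | Printed item, any/none | Printed item, graded |
|---|---|---|
| 10% v 30% | 88% | 94% |
| 20% v 50% | 54% | 98% |
| 30% v 60% | 19% | 97% |
| 40% v 80% | 5% | 99% |
| 30% v 30% (no effect) | 31% | 61% |

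The last row should be 5%. Across group sizes of nine and ten and the two readings, the false-positive rate is about 22–63%. An own-sharing item stays at about 5% in the same setting.

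**Ceiling.** P(at least one of nine others shares) = 1 − (1 − p)^9: 61% at p = 10%, 87% at 20%, 96% at 30%, 99% at 40%. With an even split and a proportion m not affirming, the largest possible w is √(m/(1 − m)): 0.33 when 90% affirm and 0.23 when 95% do. So w = 0.4 is out of reach once about 87% affirm. Whether that happens depends on p, which is unknown.

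**The case against.** The strongest reply is that the planned contrast may be between groups. Section 3.2.4 aims to capture differences between participant groups, section 3.3.2 files sharing under group dynamics, and ambassadors recruit from their own networks, so acquaintance may well differ by group. A group-worded item suits that aim, and with graded answers power is 94–99%. This stands as far as power goes. It does not rescue the test, because the same setting produces the inflated false-positive rate: there are about 10 groups, not 80–100 independent answers.

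Three stronger readings are tempting, and the documents do not support them:

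- *Nearly everyone will answer yes.* Caregiving is a set session topic ("the role and challenges of informal caregiving", section 2.1.2), so a ceiling is plausible. But no response distribution is given, the middle answer can spread responses, and at 10% personal sharing only 61% would have heard anyone. The loss of power within mixed groups does not need a ceiling.
- *Own sharing is not measured at all.* Three of the theme's four items are unseen, and one may ask it.
- *A null result would count against configurations 1b and 4b.* Their summaries in Table 1 do not name prior acquaintance as a context, and both also draw on interviews and observations.

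Members may also perceive the same group differently, so answers within a group need not be identical. A difference of that kind would concern perception, not who shared. Finally, the questionnaire is exploratory and supports the qualitative findings, which limits the damage.

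**Conclusion.** The point holds as a mismatch of level for the one printed sharing item. If acquaintance varies within groups, the respondent-level chi-square has little power. If it varies mainly between groups, the test rejects far too often under no effect. On neither reading does the power statement in section 3.3.2 apply to this item. The sizes rest on assumed sharing rates, on 10 groups of about ten, and on respondents reporting what they heard. A broad claim that the questionnaire cannot detect acquaintance effects is not established: it would need the unprinted items and a response distribution. The change is worth making because it is cheap and prevents a misleading p-value, but it concerns an exploratory component.

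**What to change.** In section 3.3.2, take this item out of the respondent-level chi-square tests. Summarise it per intervention group (for example, the share answering yes, sometimes and no) and set that descriptively against each group's acquaintance level and cultural homogeneity. State that the power figure does not cover it.

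For the individual question, whether people who know others open up more, check the full questionnaire. If an own-sharing item is there, cross that item with individual acquaintance. If it is not and forms are still open, add or reword one item to ask about the respondent's own talking, on the same three-point scale. If forms are complete, take own sharing from the planned interviews and observations; the observation guide in section 3.2.3 already records experiences shared by participants.

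Cost: one or two sentences of analysis plan, and at most one item. About 10 group-level points support description only. An own-disclosure question may be skipped more often, particularly where a fellow participant translates (section 4.1). It must also be read alongside caregiver status, since someone with no caregiving role would answer no for a different reason than a silent caregiver.
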